## Abstract

**Background:**

Earlier diagnosis followed by multi-factorial cardiovascular risk intervention may improve outcomes in Type 2 Diabetes Mellitus (T2DM). Latent phase identification through screening requires structured, appropriately targeted population-based approaches. Providers responsible for implementing screening policy await evidence of clinical and cost effectiveness from randomised intervention trials in screen-detected T2DM cases. UK South Asians are at particularly high risk of abnormal glucose tolerance and T2DM. To be effective national screening programmes must achieve good coverage across the population by identifying barriers to the detection of disease and adapting to the delivery of earlier care. Here we describe the rationale and methods of a systematic community screening programme and randomised controlled trial of cardiovascular risk management within a UK multiethnic setting (ADDITION-Leicester).

**Design:**

A single-blind cluster randomised, parallel group trial among people with screen-detected T2DM comparing a protocol driven intensive multi-factorial treatment with conventional care.

**Methods:**

ADDITION-Leicester consists of community-based screening and intervention phases within 20 general practices coordinated from a single academic research centre. Screening adopts a universal diagnostic approach via repeated 75g-Oral Glucose Tolerance Tests within an eligible non-diabetic population of 66,320 individuals aged 40-75 years (25-75 years South Asian). Volunteers also provide detailed medical and family histories; complete health questionnaires, undergo anthropometric measures, lipid profiling and a proteinuria assessment. Primary outcome is reduction in modelled Coronary Heart Disease (UKPDS CHD) risk at five years. Seven thousand (30% of South Asian ethnic origin) volunteers over three years will be recruited to identify a screen-detected T2DM cohort (n = 285) powered to detected a 6% relative difference (80% power, alpha 0.05) between treatment groups at one year. Randomisation will occur at practice-level with newly diagnosed T2DM cases receiving either conventional (according to current national guidelines) or intensive (algorithmic target-driven multi-factorial cardiovascular risk intervention) treatments.

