### Statistical methods and power calculation

Assuming a prevalence of screen-detected diabetes of 4.5%, we calculated a target of 7,000 (30% (2,100) South Asians) volunteers over three years sufficient to identify a screen-detected T2DM cohort (n = 225) demonstrating a 6% difference (80% power, alpha 0.05) between routine and intensive groups at one year assuming an intra cluster correlation coefficient of 0.14 and allowing for a loss to follow-up of 15%.

The benefits of screening and intensive treatment will be assessed using an intention to treat and allowing for clustering of patients by practice. The UKPDS CHD score at 5 years will be compared along with all secondary outcomes by treatment group, adjusting for differences in baseline variables. Estimates will be presented with 95% confidence intervals to reflect uncertainty in estimations. Sensitivity analysis assuming a range of outcomes for non-completers will be informed by baseline data. The primary perspective for the cost analysis will be the health service, with personal costs as a secondary perspective. The costs of intensive intervention will be compared with unit change in health utility at one year. Costs at one year and future costs derived from existing data will be compared with modelled risk of death and cardiovascular events, with appropriate sensitivity analysis. The cost of screening and the screening plus intensive treatment will be compared with changes in health utility from questionnaire data.

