### Funding and timescale

The project is funded for support and treatment costs by NHS Department of Health Support for Science and project grants. The screening phase of ADDITION-Leicester is now complete, having invited over 35,000 volunteers and identified 345 new cases of T2DM. As the intervention is delivered in tandem with the screening phase, the last trial visit is forecast for May 2012 assuming a mean follow up of 5 years.

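### The abstract and the statistical methods give different cohort sizes (285 and 225) for the same power claim, and the 15% loss allowance does not reconcile them

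*Protocol article*

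**What the plan says.** The Methods paragraph of the abstract says that seven thousand volunteers, 30% of them South Asian, will be recruited over three years "to identify a screen-detected T2DM cohort (n = 285) powered to detected a 6% relative difference (80% power, alpha 0.05") between treatment groups at one year. It gives no prevalence, intra-cluster correlation or loss to follow-up.

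The section on statistical methods and power calculation gives the inputs:

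- Prevalence: "Assuming a prevalence of screen-detected diabetes of 4.5" per cent.
- Screening target: "we calculated a target of 7,000 (30% (2,100) South Asians) volunteers over three years".
- Cohort: the target is "sufficient to identify a screen-detected T2DM cohort (n = 225) demonstrating a 6% difference (80% power, alpha 0.05"), again at one year.
- Clustering and attrition: "assuming an intra cluster correlation coefficient of 0.14 and allowing for a loss to follow-up of 15" per cent.

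The section on funding and timescale reports that screening is complete and has "identified 345 new cases of T2DM".

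**The concern.** Both places describe the same cohort from the same screening effort, with the same 6%, power, alpha and time point. One power claim has one sample size, and here there are two. Neither place is a change log, and nothing in the article presents the figures as alternative scenarios.

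A reader who wants to know whether the planned screening was large enough, or whether the trial met its target, needs to know which figure applies and whether attrition is already in it. The abstract's figure is also the one most likely to be cited, and it is the one shown without any of its inputs.

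**Working it through.** **Can either N be reproduced?** No. A cluster calculation for a continuous outcome needs a standard deviation, and for a relative effect also a control mean. The article gives neither, nor the sidedness of alpha. The check is therefore whether the two figures agree with each other and with the screening inputs.

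**Step 1. Does 15% loss link the two figures?**

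- 225 inflated for loss: 225/0.85 = 264.7, so 265, not 285.
- 225 with the cruder inflation: 225 × 1.15 = 258.75, so 259, not 285.
- 285 reduced for loss: 285 × 0.85 = 242.25, so 242, not 225.
- Gap: 285 − 225 = 60, which is 27% of 225 or 21% of 285. A loss of 21% would be needed to link them; the plan states 15%.

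**Step 2. What do the screening inputs yield?**

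- Cases expected: 7,000 × 0.045 = 315.
- Remaining after 15% loss: 315 × 0.85 = 267.75, so 268.

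| Stated N | Read as identified (compare 315) | Read as remaining after loss (compare 268) |
|---|---|---|
| 225 | covered | covered |
| 285 | covered | not covered, short by 17 |

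Put as volunteers needed at 4.5%:

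- 225 needs 225/0.045 = 5,000 if it is the number identified, or 225/(0.85 × 0.045) = 5,883 if it must remain after loss.
- 285 needs 285/0.045 = 6,334 if identified, or 285/(0.85 × 0.045) = 7,451 if it must remain. Only the last exceeds 7,000.

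**Step 3. What was achieved?** 345 × 0.85 = 293.25, so 293 after the planned loss. This exceeds 225 and 285 on either reading.

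**Step 4. How much does the choice matter for precision?** Assumptions of this review: 20 practices of equal size, two-sided alpha 0.05, normal approximation, N taken as the number analysed. Design effect = 1 + (N/20 − 1) × 0.14; effective N = N divided by the design effect; detectable difference in SDs = (1.96 + 0.84) × √(4/effective N).

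| N | Mean practice size | Design effect | Effective N | Detectable difference |
|---|---|---|---|---|
| 225 | 11.25 | 2.44 | 92 | 0.58 SD |
| 285 | 14.25 | 2.86 | 100 | 0.56 SD |

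For a 6% relative difference and an assumed SD of 10%, 20% or 30% of the mean, power is 82%, 30% and 16% at 225, and 85%, 32% and 17% at 285. With a fixed number of practices and a correlation of 0.14, the extra 60 people add little. The result depends far more on the SD, which is not stated, so this step cannot show which N is right.

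**The case against.** The strongest objection is that the methods section calls 7,000 volunteers sufficient to identify the cohort. That wording makes the cohort a minimum, and a minimum below the expected yield is a margin. This stands. A reader might infer that both figures are arithmetic errors because neither equals 315 or 268, or might convert 225 and 285 into yields of 3.2% and 4.1% and set these against the stated 4.5%. The article does not support that, because it never says the required cohort equals the expected yield.

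It can also be said that 225 has a natural reading: a number to be identified, with loss already allowed for. That is fair, and clearer labelling would be a courtesy if 225 stood alone. It does not explain why the abstract says 285.

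The abstract calls the 6% relative, and the methods section leaves that word out. A reader might suppose that two effect definitions lie behind two sample sizes. Nothing in the article says so, and every other element of the claim is the same.

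Finally, recruitment closed above both figures. This also stands, and it limits the consequence. A reader might infer that the contradiction puts the adequacy of recruitment, or the denominator for judging attrition, in doubt. It does not: 293 after the planned loss clears both figures, and attrition is judged against participants entered, not against a planning target.

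**Conclusion.** The contradiction holds. The article attaches 285 and 225 to one power claim, they differ by 60, and the stated loss does not connect them, so at least one is wrong. Which one cannot be settled from the article, because the SD, control mean and sidedness are not given.

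The planned 7,000 volunteers are enough for 225 on either reading. They are enough for 285 unless 285 had to remain after loss, a reading the article does not state. Nothing here shows that the screening target was too small or that the trial under-recruited.

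The consequence is limited. The 345 cases identified exceed both figures even after 15% loss, and under equal practice sizes the detectable difference moves only from 0.58 to 0.56 SD. The sample size is still a figure the trial relies on, and the correction is cheap, so it should be made.

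**What to change.** Go back to the sponsor's cluster sample-size calculation and establish which N it produced. State that one N in the abstract and in the section on statistical methods and power calculation, and say in both whether it is before or after the 15% loss. Use the same description of the 6% in both places.

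Beside it, give the expected yield (315, or 268 after loss) and the 345 cases identified (293 after the same loss), so that the margin is visible. The yield should be shown as a comparison, not as the source of the required N, which comes from the effect size, SD, intra-cluster correlation and cluster size.

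The cost is a look at the existing calculation and a correction to two sentences. No analysis, allocation or recruitment decision shown in the article changes.

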**Discussion:**

ADDITION-Leicester is the largest multiethnic (targeting >30% South Asian recruitment) community T2DM and vascular risk screening programme in the UK. By assessing feasibility and efficacy of T2DM screening, it will inform national disease prevention policy and contribute significantly to our understanding of the health care needs of UK South Asians.

**Trial registration:**

Clinicaltrial.gov (NCT00318032).

## Introduction

Type 2 Diabetes Mellitus (T2DM) is an increasingly common, potentially devastating disease characterised by prolonged asymptomatic hyperglycaemia and insidious vascular complications [1]. At present, 50% of new T2DM cases have demonstrable atherosclerosis at diagnosis and glucose abnormalities commonly characterise acute coronary and cerebro-vascular thrombotic events in people not known to have the disease [2,3]. Recent outcome studies suggest intensive glucose control among people with long-standing T2DM is associated with limited reduction in cardiovascular events, whereas sustained optimisation earlier in the trajectory of the disease may be associated with significant micro and macro-vascular benefits [4-6].

### Screening for T2DM

The frequency of T2DM, its latent presentation and potentially preventable burden of complications make it an attractive target for earlier identification and intervention through screening [7,8]. Despite convincing rationale there is in fact little evidence that this approach improves T2DM outcomes, or that treatment effective for conventionally diagnosed cases produces greater benefit if commenced within the lead time between detection by screening and clinical diagnosis [9]. Furthermore the continuous relationship between glucose concentration and cardiovascular disease well below the diagnostic threshold for T2DM [10] suggests screening programmes should include non-diabetes range hyperglycaemia (Impaired Fasting Glycaemia and Impaired Glucose Tolerance) if they are to improve population level outcomes. Primary prevention studies in these groups result in weight loss and slow progression to diabetes [11,12] supporting the concept of earlier identification and lifestyle intervention for those at risk of T2DM.

It is currently unclear how effective population screening will be at identifying people with T2DM or whether incorporating a mix of cardio-metabolic factors, including non-diabetes range hyperglycaemia, into screening programmes will substantially increase the yield of individuals at high cardiovascular risk [9]. There are additional concerns with respect to the potential adverse consequences of screening [13,14], its cost-effectiveness [15] and the magnitude of achievable cardiovascular risk reduction within this largely symptom-free population [16].

### Black and Minority Ethnic (BME) groups

Certain ethnic groups in the UK are at particularly high risk of abnormal glucose tolerance and T2DM, with reported prevalence 2-6 times that of the background white European population [17,18]. Speculated higher than average T2DM progression rates amongst UK south Asians are supported by significant global variation in reported incident cases but robust prospective data is lacking within Westernised ethnic minority populations. Studies gauging reaction to T2DM screening within these groups is also limited [19] but suggests response rates are more likely to be influenced by cultural beliefs, social stigma attached to certain conditions, and the attitude of the local community to western health care methods [20,21]. It is essential barriers to screening activity together with the effort required to overcome them are quantified if they are to inform effective planning and implementation of culturally sensitive interventions [22].

### The ADDITION study

As a result of such critical uncertainties the UK National Screening Committee currently recommend a targeted rather than universal approach, with screening confined to groups at particularly high risk of T2DM [23,24]. There is some evidence that UK general physicians are increasingly carrying out opportunistic or planned community screening of their patients [25,26]. Implementation of the National Health Service (NHS) vascular check programme recommending glucose testing for 40-70 year olds will undoubtedly further increase T2DM screening activity in the UK [27].

Priority should be directed towards developing a robust evidence base informing national policy and protecting against indiscriminate, poorly coordinated screening programmes. The results of randomised controlled trials among screen-detected cases with outcomes assessing vascular complications, health satisfaction, process of care indicators and cost are vital to this process.

ADDITION (Anglo-Danish-Dutch Study of Intensive Treatment in People with Screen Detected Diabetes in Primary Care) is a multi-centred randomised controlled trial evaluating the effectiveness of multi-factorial treatment on risk of cardiovascular disease events among over 2500 patients with screen-detected diabetes [28-30]. ADDITION-Leicester contributes to this multi-centre study but is also a stand-alone trial evaluating screening within a UK multiethnic group and quantifying the efficacy of optimised treatments on modelled cardiovascular risk over five years.

This paper describes the aims and methods of both screening and intervention phases of the ADDITION-Leicester study.

## ADDITION-Leicester Objectives

The primary aim of the ADDITION-Leicester study is to evaluate the efficacy and cost-effectiveness of 1) a universal screening programme for T2DM and 2) intensive multi-factorial cardio-protection in those identified with T2DM within a UK multiethnic population. This objective will be achieved by determining the feasibility of screening as defined by the uptake and yield achievable within a primary care setting with a known 20-30% ethnic minority (Indo-Asian) presence. The health service and patient costs of screening for T2DM and other glucose abnormalities will be evaluated, together with objective assessments of five-year cardiovascular risk and mortality. ADDITION-Leicester is registered with ClinicalTrials.gov with identifier NCT00318032.

The study consists of two phases a screening phase, employing a universal gold standard diagnostic test for T2DM and an intervention phase, delivering a randomised trial of structured cardiovascular risk intervention in screen-detected cases.

A third element, the ADDITION-Leicester pre-diabetes cohort study prospectively assesses non-diabetes range fasting and post-challenge hyperglycaemia. The aim of the ADDITION-Leicester Prediabetes Cohort Study is to determine the annual rate of progression over five years of follow up and to characterise T2DM susceptibility phenotypes.

### Methods/Design

ADDITION-Leicester adopts a community based non-selective screening approach within a representative cluster of General Practices. The study is coordinated from a regional academic centre hosted by the University of Leicester and University Hospitals of Leicester, NHS Trust but delivered in primary care through an established diabetes research network (South East Midlands Diabetes Research Network). The study is supported by competitive Department of Health project and NHS Support for Science grants. Ethical approval was obtained from the University Hospitals of Leicester (UHL09320) and Leicestershire Primary Care Research Alliance (64/2004) local research ethics committees. The study was conducted in accordance with the principles of the 1996 Helsinki Declaration. Written informed consent was obtained for all participants involved in both phases of ADDITION-Leicester study at the time of diabetes screening.

#### Study location

Volunteers were recruited from general practices in urban, suburban and rural Leicestershire, England, United Kingdom. Screening focuses upon Leicester, the county capital with an estimated population of 279,921, an ethnic minority prevalence of 32% (82% Gujarati speaking first or second generation Indo-Asians) and a local authority ranked amongst the twenty most deprived in the United Kingdom (2006 census data available at http://www.leicester.gov.uk).

### Phase 1: The screening phase

#### Identification of an eligible population: practice data handling and electronic mailers

Clinical leads from the 46 General Practices forming the Leicestershire and Rutland Strategic Health Authority were approached to participate in ADDITION-Leicester. Personalised letters were sent to the practice manager, partners and nursing staff of each practice reiterating the importance of the study to primary care, the roles of individual practices, the required commitment and the availability of remuneration for all incurred costs. A principal investigator and member of the research team visited interested practices to discuss the study in detail. 28 practices responded positively with consent for an initial database search using an extraction programme compatible with the widely used clinical EMIS (Egton Medical Information Systems Ltd, York UK) system. This specialised software generates an anonymised Master Practice List (MPL) that matches individual data to a random unique identifier (a six-digit and single letter ADDITION-Leicester number). An MPL representative of the practice population is considered essential for further participation in the study and eight practices were excluded at this stage due to data extraction failure or search software incompatibility. Practices were considered eligible if the MPL captures more than 70% of the total practice population. The MPL captures practice population demographics (age, sex, occupation, medical history, active prescriptions) and known T2DM frequency, enabling future comparison of responder/non-responder characteristics and total T2DM disease prevalence. Applying the study criteria to the MPL produces an eligible population list which is reunited with the practice dataset to provide personal details necessary to post an invitation for screening (first mailer). Those meeting the inclusion criteria are sent details of the study along with a returnable request for culturally appropriate information written in five major South Asian languages (Hindi, Gujarati, Bengali, Urdu and Punjabi). Having expressed an interest in the study, potential participants are sent individual screening appointments at either a hospital site or a mobile screening unit located within their community. Non-responders are sent a second invitation (second mailer) within six months. To ensure confidentiality is maintained practice staff handle initial database searches and mailing tasks. South Asian ethnicity is defined at this stage by forename and surname mapping using specialised software developed from census data (Nam Pehchan) [31]. Mean practice deprivation scores are calculated from individual MPL data using an Index of Medical Deprivation (IMD 2007) [32]

The size, geographical location and deprivation status of the 20 practices participating in ADDITION-Leicester is shown in Figure 1. Our calculated mean practice IMD scores match national survey deprivation quintiles and depicted practices within the Leicester city boundary appear typical of an urban UK deprivation distribution. To ensure all 20 sites are covered within the study timeframe, in six practices the entire eligible population have been sent information regarding the study whilst a random sample of the population are included in the remaining practices.

**Figure 1 F1:**
[figure not shown]
**Leicester City wards by quintiles deprivation (IMD2007)**.

Inclusion and exclusion criteria for the study are similar to the multi-centre ADDITION-Europe study [28]. Inclusion criteria are white Europeans between the ages of 40-75 years and south Asians, Afro-Caribbean's and other races between the ages of 25-75 years. A lower age cut-off for BME groups was chosen due to the reported higher risk of T2DM. People with the following pre-existing conditions are excluded (general practice diagnosis and database recorded), T2DM, terminal illnesses with a likely prognosis of less than 12 months, psychiatric illness likely to hinder informed consent, pregnancy and lactation.

#### Screening visit measurements

Standardised procedures are in place across screening sites to ensure universal gold-standard diagnostic testing for T2DM, IFG and IGT [33]. Individuals are asked to fast for eight hours prior to attending a screening appointment and to bring a list of prescribed medications with them. Before beginning the over night fast participants are asked to consume their regular evening meal and snacks, but refrain from alcohol consumption. At baseline (V0) and annual pre diabetes cohort screening visits a standard 75g oral glucose tolerance test (OGTT) is undertaken following informed consent. This test is postponed if in the preceding three days instructions to follow a normal unrestricted diet are not followed or participants report fever or unusual physical activity. On the day of testing prescribed morning medications are permitted but participants are asked not to run to their appointment or smoke until after the test. Plasma samples are obtained immediately before (fasting plasma glucose FPG) and 120 minutes after the glucose challenge (two hours post challenge glucose 120-PG) along with fasting samples for serum urea and electrolytes (UE), liver function tests (LFT), lipids (total cholesterol, LDL-cholesterol, HDL-cholesterol, triglycerides), HbA1c% (glycosylated haemoglobin) and renal function (creatinine and modification of diet in renal disease estimated glomerular filtration rate (MDRD eGFR)) (table 1). A spot urine sample for urinalysis and albumin excretion rate is also collected.

**Table 1 T1:** Summary of assessments performed at Baseline (V0), annual pre diabetes and randomised controlled trial (RCT) visits (V1-5) of the ADDITION-Leicester study

Visit	Baseline Screening (v0)	Pre diabetes annual cohort	T2DM RCT *Year 1 (v1)* *intensive/* *routine*	T2DM RCT *Year 2 (v2)* Intensive	T2DM RCT *Year 3 (v3)* Intensive* /routine	T2DM RCT *Year 4(v4)* intensive only	T2DM RCT *Year 5 (v5)* *intensive/* *routine*
